## Abstract

**ABSTRACT:**

**Introduction:**

In the UK, approximately 5.4 million adults live with asthma, of whom one in five have an uncontrolled form. Uncontrolled asthma reduces quality of life and increases healthcare use. Engaging with peers through online health communities (OHCs) can empower patients to self-manage their long-term condition. While OHCs have been in existence for several years and growing numbers of patients access them, the role of primary care in signposting patients to them has been minimal and ad hoc. We have co-developed with patients and healthcare professionals (HCPs) an intervention for adult patients with asthma, consisting of an appointment with a primary care HCP to introduce online peer support and sign patients up to an established asthma OHC, followed by OHC engagement. Feasibility work found the intervention acceptable to patients and HCPs. This protocol outlines our plan to test the intervention’s effectiveness and cost-effectiveness.

**Methods and analysis:**

An individual randomised controlled trial will be carried out. Eligible participants will be recruited via an online survey sent to adult patients on the asthma register in 50–70 general practices in several UK locations. Participants will be invited to attend a one-off, face-to-face appointment with a primary care HCP, during which they will be individually randomised to the intervention or usual care. An asthma control test (primary outcome) and other measures of clinical effectiveness will be collected at baseline and every 3 months over a 12-month follow-up period. Descriptive and inferential statistics will be used to compare outcome measures between study arms. Cost-effectiveness assessment of the intervention compared with current standard of asthma management in primary care will be reported. A sample of patients and HCPs will be interviewed at study exit and the data analysed thematically.

**Ethics and dissemination:**

The study was approved by a National Health Service Research Ethics Committee (reference: 25/NE/0006). Written consent will be obtained from all participants. Findings will be disseminated through various means, including sharing with general practices, conference presentations and peer-reviewed publications.

**Trial registration number:**

NCT06849245.

STRENGTHS AND LIMITATIONS OF THIS STUDYThe study will employ a robust mixed-methods design within a definitive randomised controlled trial (RCT) to examine the relationship between a digital social intervention promoted by primary care clinicians and outcomes.By applying qualitative, social network and sentiment analysis methods on data provided by the hosting platform of an online health community (OHC), it will be possible to thoroughly study patients’ engagement with the OHC.The study will recruit participants who are proficient in English and digitally skilled; therefore, the sample may not be fully representative of the wider asthma patient population.The primary outcome of interest, asthma control test (ACT), may be influenced by co-existing non-asthma-related conditions and can remain low despite good asthma control; therefore, we will triangulate ACT scores with other outcomes, especially asthma-related healthcare utilisation.

## Introduction

 In the UK, approximately 5.4 million adults live with asthma.^1^ About one in five of the adult population with asthma experiences an uncontrolled form of asthma.^2^ Uncontrolled asthma results in 6.3 million primary care consultations^3^ as well as 60 000 emergency hospital admissions and 200 000 hospital bed days per year.^4^ Asthma-related care costs the National Health Service (NHS) approximately £1.1 billion per year.^3^ Within the UK, mortality due to lung-related conditions is the second worst in Europe after Turkey,^5^ with 12 000 people dying from asthma between 2014 and 2024.^6^

Uncontrolled asthma often leads to comorbidities, including symptoms of anxiety and/or panic and loss of social connections,^7^,^9^ as well as lower quality of life and reduced ability to perform daily activities.^10^ Patients with uncontrolled asthma often enter a vicious cycle in which associated psychological effects and loneliness negatively influence perception of symptoms and ability to self-manage their condition, thereby further worsening self-efficacy and control of asthma.^8^,^10^

Patients’ asthma control, and associated morbidity and mortality, could be enhanced by supporting and improving self-management skills.^11^,^13^ It has been reported that engaging with peers (ie, others with similar health-related problems and/or concerns) through online health communities (OHCs) improves patients’ self-efficacy and illness understanding, thus empowering them to take responsibility for their own health and fostering their ability to cope.^14^,^17^ OHCs are increasingly being used as a means of offering and receiving online peer support.^18^ Considering their widespread adoption, OHCs could promote self-management of patients with long-term conditions at scale, thereby addressing NHS initiatives to support self-management in large cohorts of patients.^19^

There is a need for additional research on peer support interventions to establish effectiveness, acceptability and effects on health-related outcomes and inequalities.^20 21^ To date, a few studies have reported that anonymous interactions with a range of people and intuitive access to resources and tailored information and emotional support are the main benefits of engaging with an OHC.^1622^,^28^ The vast majority of claims about the usefulness of OHCs, however, are based on qualitative studies,^24 29^ while quantitative assessments of OHCs have mainly focused on studying intervention mechanisms without necessarily measuring clinical outcomes from OHC engagement.^30^,^35^

Using OHCs to access lay advice from peers is not a new concept. However, signposting patients to OHCs and online peer support as part of primary care services is a novel strategy.^36^ Previous research found that when healthcare professionals (HCPs) refer patients to studies testing digital interventions, retention rates significantly increase.^37^ It is also known that, as the primary care setting is usually the first point of contact for healthcare purposes, long-term relationships and trust are often formed between primary care clinicians and patients.^38^

We therefore envisaged the idea of primary care HCPs enabling patients who might benefit from online peer support. Together with primary care HCPs and patients with asthma, we developed the content and delivery of a two-part primary care digital social intervention.^39^ The first component consists of a structured, face-to-face appointment for adults with uncontrolled asthma, during which primary care HCPs introduce patients to online peer support and sign them up to the asthma OHC of the Asthma+Lung UK (ALUK) charity. The second component consists of actual engagement with the OHC. The ALUK asthma OHC is a well-established asynchronous text-based health forum that has around 20 000 registered and 2000 active users (ie, people who regularly use the OHC). The forum is hosted by HealthUnlocked and is moderated by HealthUnlocked staff and specialist respiratory nurses employed by ALUK.

We conducted a study to test the feasibility and acceptability of the recruitment strategy and intervention.^40^ This work demonstrated that intervention delivery was feasible and acceptable to patients in primary care settings. Patients showed, as expected, varied levels of OHC engagement. The feasibility study enabled us to refine the intervention by considering various practicalities around recruitment and delivery (eg, the importance of delivering the intervention as soon as possible following recruitment for patients to maintain enthusiasm and interest). The current protocol outlines a plan for a definitive trial to test the effectiveness of our intervention and assess its cost-effectiveness. The results will provide robust evidence regarding the benefits of promoting online peer support as part of primary care services for patients with asthma. If the intervention is proven effective and scaled up, it will enable primary care HCPs to offer it as part of routinely offered asthma services in primary care.

### Methods and analysis

### Study design

‘A survey leading to a trial’ (ie, recruiting survey to identify and invite to the trial people interested in online peer support) was selected as the best design to assess an intervention that is only likely to appeal to a subset of the asthma patient population (ie, those interested in online peer support). A randomised controlled trial (RCT) will be conducted. There will be four steps in the study: (i) a survey to identify and recruit eligible patients; (ii) a structured, face-to-face appointment to deliver the intervention or provide usual care; (iii) collection of follow-up outcome measures and (iv) one-to-one exit interviews with a sample of patients and primary care HCPs. Figure 1 schematically summarises study procedures.

**Figure 1 F1:**
[figure not shown]
Flow diagram summarising the randomised controlled trial process. OHC, online health community.

### Participants

Approximately 600 patients with uncontrolled asthma (ie, an asthma control test (ACT) score of <20) from 50 to 70 general practices will be recruited via an online survey, sent to approximately 60 000 patients on the asthma register.

To participate in the study, participants will need to:

Be adults (aged 18 years and above) on the asthma register, who have expressed their interest in digital social interventions in the recruitment survey;Report uncontrolled asthma in the recruitment survey;Be able to provide informed consent, as determined by the HCP carrying out the study appointment.

Exclusion criteria

Patients who are:

Already members of the ALUK asthma OHC or other asthma OHCs/Facebook groups (general use of social media will not prevent participation).Receiving palliative care or with very limited life expectancy (<12 months).Receiving institutional long-term care (receiving total care in residential homes or living in nursing homes).Considered unsuitable to take part in the study by their general practitioner (GP)/nurses.

### Recruitment processes

Assistance in identifying general practices willing to act as recruitment sites will be sought from four National Institute for Health and Care Research Regional Research Delivery Networks (NIHR RDNs): North London, South London, South Central and East of England); further RDNs may be approached, if necessary. Nurses’ groups (eg, from the Primary Care Respiratory Society, or London Respiratory Nurses) might also be approached to identify practices interested in joining the study.

All eligible adults on the asthma register will be identified through searches on the clinical record systems (performed by practice-based staff) at the general practices. A text message will be sent to patients directly from the clinical record system or through AccuRx (ie, an NHS-approved software provider used by primary care professionals to contact their patients). This text message will include a link to a short online survey. The survey will act as a recruitment tool and will also include a link to the Participant Information Sheet (PIS). Patients will be given a deadline of 1 month to fill in the survey and a single reminder text message will be sent, 1 week before the deadline. Posters and/or leaflets will also be displayed at participating general practices, including a QR code link to the recruitment survey.

Eligible patients will be invited to a structured, face-to-face appointment with a primary care HCP to receive the intervention or usual care. Invitation and relevant arrangements for the appointment will be made by general practice staff supported by the research team (through text messages/phone calls/emails). A mutually convenient time for the HCP and the patient will be established.

### Study procedures

#### Recruiting survey

The survey includes a screening section, asking patients to confirm they have an asthma diagnosis and are over 18 years, followed by questions establishing their eligibility for the trial (ACT questionnaire, membership of online asthma forums/Facebook groups and interest in taking part in the trial), with an additional section about support with managing their asthma. Eligible respondents will be asked to provide their contact details. Survey and study data will be recorded using Research Electronic Data Capture (REDCap) software, a secure application for designing and managing online surveys and databases. Completion of the recruiting survey is anticipated to take <5 min (see online supplemental material 1 for a copy of the recruiting survey).

#### Structured appointment

All participants will be invited to attend a one-off, face-to-face appointment with a primary care HCP (most likely a general practice-based nurse or pharmacist) at their general practice, lasting 30–45 min depending on whether they receive the intervention or usual care only, where baseline data collection and randomisation will be undertaken. Participants will be individually randomised to either receive the intervention or to receive usual care. Those allocated to the intervention arm will be introduced to the intervention (see 'Intervention arm' section below). All HCPs involved will complete an online training course designed by the research team, covering all aspects of the face-to-face appointment delivery (including data capture in REDCap, randomisation, how to explain the control arm of the trial and how to introduce online peer support and motivate intervention arm participants to engage with the OHC).

#### Randomisation

The randomisation ratio to both treatment arms will be 1:1. During the face-to-face appointment, the HCP will use a randomisation tool embedded in the study database on REDCap to determine group assignment (intervention or control) for each participant. Randomisation lists will be prepared prestudy commencement using a permuted block approach in which the number of allocations is 50:50 within each block, the size of which is determined randomly from possible block sizes of 4, 6 or 8. The sequence of allocations within a block is randomly permuted, conditional on the 50:50 allocation requirement (so a block of size 4 gives rise to the following six possible sequences of allocations: AABB, ABAB, ABBA, BAAB, BABA and BBAA). Allocation will be stratified by asthma severity, based on ACT score (two groups: lower (ACT <12), higher (ACT ≥12) to 19) and age (two groups: low (age 18–49 years), high (age 50–99 years)) such that each stratum (ie, combination of asthma severity group and age group) has its own randomisation list, so ensuring balance of these factors between the treatment groups. Blinding will not be possible for HCPs and patients. The central research team will also be unblinded as members will need to contact patients for interim follow-ups and reminders.

#### Intervention arm

After the collection of baseline measures, the face-to-face appointment with participants in the intervention arm will involve:

Signposting to the ALUK asthma OHC by offering a ‘tour’ of the OHC and explaining the different sections of the website.An introduction to norms and values for passive (just reading) and active (writing OHC posts) participation.Explaining the differences between posting publicly and privately (public posts are shared, according to HealthUnlocked terms and conditions, with third parties whereas private messages can be sent via the chat function and are not shared).Motivation for engagement with the OHC to seek and offer self-management information and support, by emphasising that the OHC could be used ad hoc (eg, when feeling unwell or when emotional support is needed).Problem solving with respect to any difficulties/concerns.Signing patients up to the OHC, by explaining terms and conditions of HealthUnlocked.

To sign up participants, HCPs will ask them to use their own mobile phone/other electronic device and access a study-specific landing page provided by HealthUnlocked, outlining the consenting process to the OHC and containing a privacy notice. This allows easy onboarding by default opting out participants from any sharing of collected data with third parties. Participants will need to provide their email address and will be invited to choose an anonymous username. Participants’ email addresses will not be visible within the OHC.

Participants will leave the face-to-face appointment with a card with a QR code link to the ALUK OHC on one side and to the study website/contact details on the other side and a reminder of their username and password (data not recorded for the study). Once logged into the OHC, participants will have the opportunity to change their username/password as well as any other settings in their account (eg, opting in for receiving HealthUnlocked emails).

Depending on the availability of resources, monthly text messages might be sent to participants who have consented, reminding them to engage with the OHC.

#### Control arm

After the collection of baseline measures (same measures to the intervention arm), control group patients will go back to receive usual care only without any reference to OHCs and online peer support.

### Outcomes and measures

Twelve months following the face-to-face appointment, all participating patients will receive a text message and/or email with a link to an online survey collecting follow-up measures (up to three reminders will be sent). In addition, patients who have consented to receiving regular contact will be telephoned by a member of the research team every 3 months during the 12-month follow-up period to collect data on asthma control, quality of life and care utilisation.

The primary outcome of interest will be ACT score collected every 3 months for 12 months following the face-to-face appointment (adjusted for baseline value in the analysis). Secondary outcomes will include variables related to the overall health and well-being of the patient, as well as associated care utilisation (table 1). In addition to outcomes self-reported by patients (table 1), non-self-reported outcome variables will be obtained (table 2), depending on data availability and consent for access to healthcare records.

**Table 1 T1:** Outcomes self-reported by participants

Domain	Outcome	Measure	Baseline*	3 months†	6 months†	9 months†	12 months‡
Clinical factors	Control of asthma§	ACT questionnaire	X	X	X	X	X
	Asthma exacerbations over last 3 months	Bespoke question	X	X	X	X	X
	Adherence to medications	MARS-10 questionnaire	X				X
Quality of life	Health-related quality of life	EQ-5D-5L questionnaire	X	X	X	X	X
Healthcare use and time off work (economic factors)	Primary and secondary care use over last 3 months	Bespoke question	X	X	X	X	X
	Time off work to seek care and/or due to asthma over last 3 months	Bespoke question	X	X	X	X	X
Psychosocial factors	Depression	PHQ-8 questionnaire	X				X
	Anxiety	GAD-7 questionnaire	X				X
	Self-efficacy	General Self-Efficacy Scale	X				X
	Smoking status	Bespoke question	X				X
OHC use factors (only related to intervention arm participants)	Amount and type (passive vs active) of OHC engagement	Bespoke question					X
Internet use for health support	eHealth literacy	eHealth Literacy Scale	X				
	Interest in and appropriateness of digital social interventions in primary care	Bespoke question	X				

* At the time of the study-related face-to-face appointment.

† Interim follow-up at 3, 6 and 9 months following the face-to-face appointment, data collected over the telephone by the research team.

‡ Final follow-up survey 12 months following the face-to-face appointment, survey self-completed by participants.

§ Primary outcome.

ACT, asthma control test; EQ-5D-5L, EuroQol 5-Dimensions 5-Level version; GAD-7, Generalised Anxiety Disorder 7-item scale; MARS-10, 10-item Medication Adherence Rating Scale; OHC, online health community; PHQ-8, 8-item Patient Health Questionnaire depression scale.

**Table 2 T2:** Non-self-reported outcomes of interest

Outcome	Data source	Baseline*	12 months†
Number of asthma exacerbations over last 12 months	Discovery‡ and/or NHS Digital§	X	X
Primary and secondary care health service utilisation and associated costs over last 12 months	Discovery‡ and/or NHS Digital§	X	X
OHC engagement metrics (ie, amount of engagement, communities joined, number of logins, number of likes and time spent on pages), public posts and metadata, including time of post, thread and user details (outcome only related to intervention arm participants)	ALUK OHC data (provided by the manager of the OHC platform)		X

* At the time of the study-related face-to-face appointment.

† 12 months following the face-to-face appointment.

‡ Discovery is a clinical partnership project in East London to link primary and secondary care records, by creating a single database.

§ NHS Digital is a national provider of health-related data setting out to transform and improve healthcare in the UK.

ALUK, Asthma+Lung UK; NHS, National Health Service; OHC, online health community.

Patient data at baseline and interim follow-up will be collected and recorded directly in the online study database by the HCPs carrying out the face-to-face appointment and the research team, respectively. The final follow-up survey 12 months after the face-to-face appointment will be self-completed by participants (completion should take approximately 10 min).

### Exit interviews

At the end of the study, patients and HCPs involved will be invited to participate in a one-to-one, semi-structured, virtual exit interview. A convenience sampling approach, based on patients and HCPs who are available and willing to take part at the end of the study, will be used. Recruitment will continue until data saturation. Invitations will be made through a phone call/email/text message by the research team. A mutually convenient time for the interview will be agreed. If interviewees wish, reminder phone calls/emails will be made/sent.

Interviews will be undertaken by members of the research team and/or by appropriately trained members of the Centre for Applied Respiratory Research, Innovation and Impact (CARRii) patient and public involvement (PPI) group, remotely via Zoom or Microsoft Teams. Each interview will last up to 60 min. An interview schedule will be used (online supplemental material 2). In these interviews, we will explore patient and HCP views about their involvement in the study and receiving/delivering the intervention. All interviews will be digitally recorded, subject to consent, through recording functions in Zoom/Teams platforms.

Figure 2 provides an overview of the procedures each participating patient will have to undergo in this study.

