### Sample size justification

It is estimated that a sample size of 586 patients (293 per arm, allowing 20% loss to follow-up) is needed for 90% power to detect a standardised effect size of 0.3 (equivalent to a difference from baseline to 12-month follow-up in ACT score of 1.05), assuming an SD of 3.5.^41^ This gives a total of 234 patients per arm with completed follow-up data. In the previous feasibility study, we had a 10% response rate in the recruiting survey and a recruitment rate (ie, proportion of survey respondents consenting to and receiving the intervention) of 9.8%. Assuming response and recruitment rates are similar in the RCT, the survey will need to be circulated to just over 59 000 patients (see figure 1 for detailed calculation).

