### Analysis of qualitative data from exit interviews

Audio-recordings from the exit interviews will be transcribed *verbatim* by a professional transcribing agency and analysed thematically using the six stages of reflexive thematic analysis by Braun and Clarke.^48^ Both inductive and deductive approaches will be employed in thematic analysis coding. Coding schemes as well as themes and subthemes will be informed by social support theory (as framed by Dennis^49^) and will aim to synthesise and interpret experiences of the intervention’s delivery and participation in the study in general. Attention will be paid to identifying ‘direct’ effects (ie, directly impacting health-related outcomes), ‘buffering’ effects (ie, reducing the detrimental influence of stressors on health) and ‘mediating’ effects (ie, indirectly influencing health via cognitions, emotions and behaviours) in the interview data. These represent the main ‘effect models’ (ie, mechanisms resulting in beneficial outcomes) underpinning peer support interventions, as outlined in Dennis’s model.

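### Convenience sampling for the exit interviews risks under-representing intervention participants who never used or stopped using the online health community

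*Protocol article*

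**What the plan says.** In the protocol article, the Exit interviews section states who is approached and when: "At the end of the study, patients and HCPs involved will be invited to participate in a one-to-one, semi-structured, virtual exit interview". Selection is by "A convenience sampling approach, based on patients and HCPs who are available and willing to take part at the end of the study". The stopping rule is: "Recruitment will continue until data saturation". No quota or stratum by arm, by level of OHC use or by withdrawal is given, and the choice is not deferred to another document.

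The interviews have two uses. The Exit interviews section says that "we will explore patient and HCP views about their involvement in the study and receiving/delivering the intervention". The section on analysis of the interview data adds mechanism: "Attention will be paid to identifying ‘direct’ effects (ie, directly impacting health-related outcomes", followed by buffering and mediating effects.

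The Introduction reports from the feasibility study: "Patients showed, as expected, varied levels of OHC engagement". Table 2, under Outcomes and measures, lists "OHC engagement metrics (ie, amount of engagement, communities joined, number of logins, number of likes and time spent on pages" for intervention participants at 12 months. Table 1 adds a self-reported question on amount and type of OHC use at the same time point.

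**The concern.** Use of the OHC is voluntary and presented to patients as ad hoc, so some intervention participants will never use it and others will stop. A sample of whoever is free and willing at study end has no step that ensures these people are heard. Saturation does not repair this: it shows that the people interviewed have stopped raising new themes, not that the people who were not interviewed would have raised none.

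The stake is explanatory. If the difference in asthma control test (ACT) score is null or small, a central question is why people did not engage or did not continue. Platform data can show that a participant stopped logging in, but someone who never logs in leaves no posts to analyse. The reasons have to come mainly from asking. The limitations in the article acknowledge self-selection into the trial by digital skill and interest, but not self-selection into the interviews.

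**Working it through.** **1. The sections side by side.**
- Introduction: varied engagement is expected; no proportions are given.
- Quantitative analyses: engagement matters enough to define the per-protocol set (use at least once in each of three consecutive months).
- Table 2: engagement metrics will be held for the intervention arm at 12 months.
- Exit interviews: none of this enters the choice of interviewees.

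The information needed to select by engagement is therefore already collected, at about the time the interviews take place.

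**2. The plan's own figures.** No number is stated for the interviews, so the only figure to reproduce is the trial sample size. Inputs from the Sample size justification: difference 1.05, SD 3.5, power 90%, "allowing 20% loss to follow-up". Two-sided alpha of 0.05 is my assumption; the article does not state it.
- Standardised effect: 1.05 / 3.5 = 0.3.
- n per arm = 2 × (1.960 + 1.282)² / 0.3² = 233.5, rounded up to 234.
- 234 / (1 − 0.20) = 292.5, rounded up to 293 per arm, 586 in total.

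The stated figures reproduce. The allowance for missing 12-month data is 293 − 234 = 59 per arm. This does not count people who left the OHC, nor people who cannot be interviewed.

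**3. What selective uptake could do (illustration on assumed rates only).** Let q be the share of the intervention arm who are not persistent users, and r their uptake of the interview relative to persistent users. Their share of that arm's interviewees is q·r / (q·r + 1 − q). For example, q = 0.5 and r = 0.5 gives 0.25 / 0.75 = 33%.

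| q | r = 1 | r = 0.75 | r = 0.5 | r = 0.25 |
|---|---|---|---|---|
| 30% | 30% | 24% | 18% | 10% |
| 50% | 50% | 43% | 33% | 20% |
| 70% | 70% | 64% | 54% | 37% |

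With r = 1 there is no distortion.

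**4. The same formula where persistent users are a minority.** Let p be the share of persistent users, assumed 2 to 3 times as willing to be interviewed.
- p = 20%: they form 0.4 / 1.2 = 33% to 0.6 / 1.4 = 43% of interviewees, leaving 57% to 67% who are not persistent users.
- p = 30%: they form 0.6 / 1.3 = 46% to 0.9 / 1.6 = 56%, leaving 44% to 54%.

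Persistent users are over-represented in each case, but the others still make up about half of the sample or more. How far the sample is tilted depends entirely on two quantities that the documents do not give.

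**The case against.** The case on the other side is substantial.

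- **The direction is inferred, not shown.** The documents give no interview uptake and no engagement proportions. Dissatisfied participants may also be keen to talk. This stands, and it limits the claim to a risk.
- **Non-users are not excluded.** The invitation goes to the patients involved, whether or not they used the OHC. It is made by phone, email or text, for a remote interview at an agreed time, and pays £30. Someone who stops using the OHC has not left the trial. This stands too.
- **Mechanism does not rest on interviews alone.** OHC activity data linked to health data, measured mediators and regressions on engagement are planned, and healthcare professionals are interviewed. These sources can show who disengaged, but say much less about why, so this answers the point only in part.
- **Convenience sampling is a disclosed choice in a secondary component.** True. But it is made in the text, and a better method is available from data already collected.

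Two stronger readings are tempting. A reader might infer that the 59 per arm allowed for loss cannot be interviewed. The documents do not support that: the 59 are an allowance for missing 12-month data, the interview is a separate invitation, and a participant who misses the survey may still be reached. The article does not say whether withdrawn patients are invited. A reader might also infer that the interviews will give a favourable picture regardless of the trial result. Nothing in the documents shows this, and the last step of the working shows that non-persistent users could still be the majority of interviewees.

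**Conclusion.** The concern holds as a risk. Convenience sampling at study end, with saturation as the only stopping rule, may under-represent intervention participants who never used or stopped using the OHC, and so weakens what the interviews can say about non-engagement and mechanism. The size of the risk cannot be computed from the documents. The illustration runs from no distortion under equal uptake to, for example, a fall from 50% to 20% of interviewees if non-persistent users are half the arm and a quarter as willing; all of these rates are assumed. The randomised comparison, the primary outcome and the sample size are not affected. The point is worth acting on because the improvement is cheap and bears on how a null or small effect would be explained.

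**What to change.** In the Exit interviews section, replace convenience sampling of patients with purposive (maximum-variation) sampling at study end:

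- Select by arm and, within the intervention arm, by engagement level: none, stopped, sustained passive, sustained active. Use the HealthUnlocked metrics already due at 12 months, and write down the definitions of the levels before inviting anyone.
- Set a small minimum number for non-users and stoppers within the same overall number of interviews.
- Invite participants who missed the 12-month survey, unless they have declined contact.
- Report interviewees' engagement alongside that of the whole intervention arm, so that readers can see how far the two differ.

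I would not ask for saturation within every engagement group, which would need more interviews. Nor would I ask for interviews with leavers during follow-up: the trial is unblinded with a self-reported primary outcome, and such contact could affect later engagement or reporting.

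The cost is one revised paragraph and somewhat slower recruitment of non-users. No new data, staff or payments are needed. The metrics must be available before invitations go out, and the team should confirm that the consent wording, which is not shown here, covers using them to select interviewees.
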